### Data collection

1. Senior health periodic examination at HEC

a. Socio-demographic data

Age, sex, marital status, address, economic affluence and vulnerability level (evaluated with the EPICES score, the individual index of deprivation used at the HEC [20]) were recorded.

a. Clinical data

We recorded weight, height, the number of different daily therapeutic groups attended, psychotropic dose (established by asking the patient or reading their last prescription), autonomy (evaluated by testing four activities of daily life [21]), and mood (evaluated using the Mini-Geriatric Depression Scale (mini-GDS) [22]).

a. Para-clinical data

Data recorded included long sighted visual acuteness (evaluated using the Monoyer scale), an evaluation of balance and walking (using tests such as the Timed Up and Go (TUG) [23] and the imagined TUG), patient proprioception sensitivity (measured using the diapason test), and the results of the handgrip test, unipodal position evaluation, chair rising, temporal analysis of walking and posture analysis (at the HEC of Lyon and Angers).

a. Memory complaint

A self-questionnaire composed of binary questions (Q1) was used to assess memory at the HEC Angers and Saint-Etienne. A questionnaire (Q2) was carried out by the doctor at the HEC of Lyon (Table 1). At least one positive answer to the questionnaire was required for the subject to be included in the study.

a. Cognitive testing performed

The EVATEM study assessed Dubois’ five-word test [24], the cognitive disorders examination test (CODEX) [25,26] and the verbal fluency test [27]. These tests were chosen as they assess verbal memory, temporal and spatial orientation and executive function but are straightforward and rapid.

Dubois’ five-word test is an episodic memory test where subjects are asked to learn five words belonging to different semantic groups and lacking phonetic similarity (for example: beverage, cooking tool, vehicular, building and insect) with control of the encoding. The test is built in such a way that it enables differentiation between symptoms of hippocampus damage (associated with AD) and common memory impairment; it includes immediate free recall exercises and postponed free recall activities. In the case of recall difficulty, a cue is suggested.

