**Figure 2 F2:**
[figure not shown]
**EVATEM study flowchart.** MC: Memory Complaint, ES: elderly subjects. A: Angers, SE: Saint-Etienne, L: Lyon.

A total of 4571 elderly subjects aged 65 years or over were eligible for research into the diagnosis of memory complaints. Amongst those subjects, 57.5% were recruited by the HEC of Lyon, 34.2% by the HEC of Angers and 8.3% by the HEC of Saint-Etienne.

The percentage of subjects with memory complaints, detected using the self-administered questionnaire (Q1), was 70% for the HEC of Angers and 59.4% for the HEC of Saint-Etienne. At the HEC of Lyon, where memory complaints were screened using a questionnaire administered by doctors (Q2), the percentage of complaints was 27.5%. Cognitive tests were refused by 33.6% of people with memory complaints. Amongst the 832 subjects for whom an appointment at MC had been made, 74.5% attended a consultation. Thus, the final study population included 620 subjects.

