## Discussion

The EVATEM study will identify which one, or which combination, of these studied tests are the most predictive of MCI and AD and related disorders. This will provide a recommendation as to which should be performed on elderly patients reporting a memory complaint during a health examination at HEC.

The age for inclusion selected for the EVATEM study was 65 years old and more as the prevalence of AD is low before the age of 65 years [53]. This age criterion was also used in the PAQUID study [54] and in a three city study [55].

HEC recruit elderly patients from those listed in the files of the French health insurance system. Previous studies have compared elderly individuals using HEC to those of the general population of the same age. It appears that people over 60 years old who consult at HEC are more likely to be young male seniors (60 to 70 years old), living in couples, individuals with a healthy lifestyle (lower tobacco consumption, lower alcohol consumption and more physic activity) and those that consult more frequently than the corresponding general population (data unpublished, CETAF). However, it was previously thought that the population attending HEC was not fundamentally different from the general population of elderly persons aged over 60 years who were living at home and not suffering from disabilities.

The fact that patients agreed to participate to a periodic examination suggests that they take an interest in their health and may therefore also be more likely to attend cognitive impairment screening. Use of the Q1 questionnaire may lead to a self-selection bias associated with the fear of diagnosis, especially if another family member is suffering from AD. Representations of this type of disease and people with AD in our society are extremely negative. Consequently, patients may delay, as long as possible, addressing the issue of a disease that “crystallizes all the fears associated with aging” [6]. Societal representations lead to denial behavior and avoidance of medical consultations as the fear of diagnosis is associated with a set of losses including identity and dignity [56,57]. The administration of Q2 by doctors from Lyon led to a high selectivity in the screening of memory complaints. It will be interesting to compare the diagnostic and predictive values of the tests that result from these two groups.

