This study, which began in late 2009, is based on the 1984 criteria for the clinical diagnosis of AD. In the revised NIA-Alzheimer’s Association criteria (May 2011), a semantic and conceptual distinction is made between AD pathophysiological processes and the clinically observable syndromes that result (this distinction was blurred in the 1984 criteria [58,59]). According to the revised criteria, the clinical and cognitive evaluation for MCI due to AD is almost identical to the one previously described by Petersen *et al.*[59]. All patients who would have been classified under “probable AD” by the 1984 NINCDS–ADRDA criteria would be likely to meet the current criteria for probable AD dementia. The predictive values of the three cognitive tests for the diagnosis of a mild amnesic cognitive impairment, in turn predictive of AD, will be analyzed.

The use of cognitive tests can be limited by language barriers; only people with a good level of French had been included in EVATEM. There were a particularly high number of exclusions in Lyon and it would be interested to develop a translation of the selected tests.

This study provided an opportunity for each HEC to establish care pathways with their closest MC and for medical and paramedical staff to be educated in the early diagnosis of related disorders [5]. Specific training, carried out by MC geriatricians, was required. This was well received and has demonstrated that cognitive tests can be easily integrated into a preventive consultation.

The participants of this study will be re-examined one year after their inclusion; this will enable us to estimate the predictive abilities of the tests to diagnose MCI and dementia. The use of simple tests with good predictive abilities should help guide patients from centers of prevention to MC for early medical and behavioral care management.

Further research projects are planned using the EVATEM database. These include studying the relationships between insecurity and memory complaints, cognition and anxiety-depression, cognition and walking, and cognition and vitamin D levels.

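### Minor: the suggested Q1-versus-Q2 comparison is the same contrast as Lyon versus the other two centres, so it supports no inference about the questionnaire

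*Protocol article*

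**What the plan says.** Under Data collection (memory complaint), the protocol article assigns the screening questionnaires by centre. For two centres: "A self-questionnaire composed of binary questions (Q1) was used to assess memory at the HEC Angers and Saint-Etienne". For the third: "A questionnaire (Q2) was carried out by the doctor at the HEC of Lyon". Table 1 shows that the two instruments differ in content (six items against five) as well as in who administers them.

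The Inclusions section reports the share of subjects with a memory complaint. With Q1 it "was 70% for the HEC of Angers and 59.4% for the HEC of Saint-Etienne"; with Q2 at Lyon it was 27.5%.

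The Discussion then makes two statements. The first is causal: "The administration of Q2 by doctors from Lyon led to a high selectivity in the screening of memory complaints". The second follows directly: "It will be interesting to compare the diagnostic and predictive values of the tests that result from these two groups".

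The Statistical analysis section does not list this comparison. It provides for regression models adjusted for potential confounders, which it does not name.

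**The concern.** Questionnaire is fully determined by centre, and only one centre used Q2. Any difference in sensitivity, specificity or predictive values between the two groups would therefore carry everything else that distinguishes Lyon from Angers and Saint-Etienne. The document itself records several such differences, some of them in the reference work-up against which the tests are judged. The Discussion does not mention centre as a rival explanation, either where it credits Q2 with the selectivity at Lyon or where it suggests the comparison.

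At stake is what may be concluded. A difference read as an effect of how the complaint was elicited would have no support, and a finding of no difference would be just as hard to interpret, since questionnaire and centre effects could offset each other. Predictive values are especially exposed, because they move with the prevalence of impairment among those tested, and that may differ between centres for reasons unrelated to the questionnaire.

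**Working it through.** **Step 1: inputs and a check on them.** The Inclusions section gives 4571 eligible subjects, with shares of 57.5% (Lyon), 34.2% (Angers) and 8.3% (Saint-Etienne), and complaint rates of 27.5%, 70% and 59.4% respectively. The counts below are approximate because the percentages are rounded.

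- Lyon: 4571 × 0.575 = 2628.3 eligible; × 0.275 = 722.8 complaints
- Angers: 4571 × 0.342 = 1563.3 eligible; × 0.70 = 1094.3 complaints
- Saint-Etienne: 4571 × 0.083 = 379.4 eligible; × 0.594 = 225.4 complaints

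The sum, about 2042, agrees with the 2041 complaints stated in the Abstract to within rounding. The centre figures can be used.

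**Step 2: can a questionnaire effect be estimated?** Code Q = 1 for Q1 and 0 for Q2, with indicators A (Angers) and S (Saint-Etienne) and Lyon as reference. The rows (intercept, Q, A, S) are:

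- Lyon: 1, 0, 0, 0
- Angers: 1, 1, 1, 0
- Saint-Etienne: 1, 1, 0, 1

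In every row Q = A + S. The matrix has four columns and rank 3, so a questionnaire coefficient cannot be estimated alongside centre. More subjects from the same three centres would add copies of these rows and leave the rank at 3. Adjusting for patient characteristics does not remove the identity either.

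**Step 3: what else changes with centre?**

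- Each city has its own academic memory clinic making the diagnosis (Study design).
- MRI was systematic at Angers, but limited to subjects with detected anomalies at Lyon and Saint-Etienne (Examination procedure).
- Lyon alone added an anxiety scale, a compliance questionnaire and a nutritional assessment (Examination procedure).
- On exclusions, in a paragraph about language, the Discussion says: "There were a particularly high number of exclusions in Lyon".

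**Step 4: how far do centres differ under the same questionnaire?** Angers and Saint-Etienne both used Q1.

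- Difference: 0.700 − 0.594 = 0.106
- Standard error: √(0.70 × 0.30/1563.3 + 0.594 × 0.406/379.4) = 0.0277
- 95% CI: 0.106 ± 1.96 × 0.0277, or 5.2 to 16.0 points; z = 3.8 (4.0 with a pooled variance)

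**Step 5: the Q1-Q2 gap, for scale.**

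- Pooled Q1 rate: (1094.3 + 225.4)/(1563.3 + 379.4) = 67.9%
- Gap from Lyon: 67.9 − 27.5 = 40.4 points
- By centre: Angers minus Lyon 42.5; Saint-Etienne minus Lyon 31.9
- The within-Q1 gap is 10.6/40.4, about a quarter of the Q1-Q2 gap

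Step 4 shows that complaint rates vary between centres with the questionnaire held fixed. It does not measure how much of the 40-point gap is due to centre; nothing in the data can.

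**The case against.** The strongest reply is that the text claims little. The comparison appears once, in the Discussion, as something of interest. It is not an objective in the Background, not an outcome under Main outcome measure, and not an analysis under Statistical analysis. That is right, and it limits the weight of the point.

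A reader might infer that the protocol already attributes a difference in test performance to the questionnaire. It does not. Its causal statement concerns only the selectivity of complaint screening, and it reports no test-performance result. A reader might also infer that a choice between Q1 and Q2 hangs on the outcome. The recommendation announced in the Discussion concerns which cognitive tests to perform; nothing proposes choosing a questionnaire. Nor does the document compare the populations of the three centres, so a difference in population cannot be asserted as fact.

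It can further be said that both Q1 centres have more than twice Lyon's complaint rate, and that the article names Lyon and its doctors alongside Q2 and reports rates by centre, so the overlap is in plain view. As a description of Lyon, high selectivity stands. The cause of it is not established, however, and the article does not discuss the overlap.

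What remains after all this is the lack of identifiability. It is not a detail an article may leave to a fuller plan, because no analysis plan can make the questionnaire effect estimable from these three centres.

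**Conclusion.** The point holds as a minor one. The Q1-versus-Q2 contrast and the Lyon-versus-other-centres contrast are the same, so neither the causal wording about Q2 nor any later comparison of test performance between the two groups can support a statement about the questionnaire. Complaint rates differ by 10.6 points (95% CI about 5 to 16) between two centres using the same questionnaire, so centre differences are a demonstrated rival explanation.

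The identifiability conclusion rests only on the stated assignment of questionnaires to centres. The interval treats subjects as independent and uses counts rebuilt from rounded percentages.

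Two stronger readings are not supported. The result does not show that Q2 had no effect at Lyon; it shows that the effect cannot be isolated. It also does not touch the pooled main analysis or the sample size, neither of which depends on this contrast.

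**What to change.** In the Discussion:

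1. Replace the causal verb about Q2 with an association: complaint rates were lower at Lyon, where Q2 was used.
2. In place of a Q1-versus-Q2 contrast, say that test performance will be reported descriptively by centre, in three strata. Angers and Saint-Etienne, which shared Q1, then show the reader how far results vary with the questionnaire held fixed.
3. State that questionnaire and centre cannot be separated and that no inference about the questionnaire will be drawn.

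If item-level answers were stored, restricting to subjects positive on item 1, which is similar in the two questionnaires, could be an optional descriptive check. It is no remedy, because it leaves both centre and mode of administration confounded; and the document does not say that item answers were kept.

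The cost is a few sentences and a by-centre table. The study gives up any claim about the questionnaires. The Saint-Etienne stratum, at 8.3% of eligible subjects, will probably be imprecise.

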## Abbreviations

AD: Alzheimer’s disease; ANOVA: Analysis of variance; BEM 144: Battery for mnesic efficiency; BORB: Birmingham object recognition battery; CAB 96: Cognitive assessment battery; CETAF: Centre Technique d’Appui et de Formation des Centres d’Examens de Santé; CODEX: Cognitive disorders examination; DHOS: Direction Générale de l’Offre de Soins; DO 80: The picture naming test; FAB: Frontal assessment battery; HEC: Health examination centers; IAD: Instrumental activities of daily living; MC: Memory clinic; MCI: Mild cognitive impairment; Mini-GDS: Mini-geriatric depression scale; MMSE: Mini-mental state examination; MRI: Magnetic resonance imaging; PV: Predictive values; RMSO: Regional medical service officer; ROC curve: Receiver operator characteristic curve; SPSS: Statistical package for the social sciences; TSH: Thyroid stimulating hormone; TMT: The trail making test; TUG: Timed Up and Go; VOSP: The visual object and space perception battery; WAIS: Wechsler Adult Intelligence Scale
